### 3. Conceptual frameworks

In order to assess the effects, implementation outcomes and influencers of the data use initiative in the primary health care settings we use a conceptual framework that acknowledges that improving health information systems [23] in the primary health care settings can improved data use and therefore strengthen the primary health care, improve quality of care and health outcomes (see Fig 1).In addition, we acknowledge the contribution of the capability, opportunity, motivation and behavior (COM-B) model in changing behaviors of organizations and individuals to be favorable for data use in the primary health care settings. Our conceptualization is also inspired the implementation science frameworks that include: 1) Conceptual Framework for Implementation Outcomes [24], in this study, we consider all the three outcomes of implementation research namely, implementation outcomes, service outcomes and client outcomes 2) Reach, Effectiveness Adoption Implementation Maintenance (RE-AIM) framework [25] 3) Consolidated Framework for Implementation Research (CFIR) [26]. Additional guidance for specific constructs are derived from the fidelity of implementation framework [18], theoretical framework for acceptability [27].

**Fig 1 pone.0303552.g001:**
[figure not shown]
Theory of change for data use in primary health care.

### 4. Study components

The steps to conduct this study will be based on the two main components of the study, that is , effectiveness and implementation process .The effectiveness component entails collecting data to measure outcomes of the initiatives on selected indicators (top level indicators for service areas such as maternal, newborn, adolescents and child health ) at PHC before and one year after the implementation of the program .The implementation process study aims at understanding how the program is implemented amid contextual influences. To complete the components, the study will adopt the following steps.

#### 1) Develop a theory of change (TOC) for data use initiatives and document the process under which such a TOC is developed

In order to understand the mechanism through which outcomes of data use initiatives are produced, we follow the implementation science steps throughout the conduct of this study. The steps are 1) developing the theory of change (TOC by reviewing internal program documents, attendance to various meetings on the data use initiatives and consultations with program developers and implementation teams and literature review on similar programs targeting primary health care settings 2) Testing the TOC, by developing tools and collecting empirical data in the field 3) Refining the TOC through a qualitative work consisting of in-depth interviews with key stakeholders involved in, or who have a stake in data use initiative, and focus groups and in-depth interviews with program beneficiaries, i.e., the health care mangers and frontline health care workers. The initial TOC has been developed (see Fig 1 & S1 File for a details) in order also to guide the development of data collection tools at all stages of the study.

#### 2) Understand the initial (baseline) situation of data use in the study settings in relation to decision making and comprehensive (council or health facility) planning

To understand the baseline situation, the four councils implementing the data use initiative will be matched equally with comparable councils where the data use interventions will not be implemented. Stratified sampling (to distinguish the level of facilities) will be used in these four councils to select a representative sample of facilities to be observed for one year after the project is implemented. This step combines quantitative and qualitative methodologies to evaluate the current state of data use in the recipient health facilities.

#### 3) Understand the implementation processes (acceptability, adoption, fidelity and sustainability) of the data use initiatives amid the influence of contextual factors

Complex interventions are often criticized as being a black box because it is difficult to know exactly why an intervention did (or did not) work. To address this gap and open the black box, a process evaluation will be completed using a convergent parallel mixed methods design to assess acceptability, adoption, fidelity and maintenance of the intervention processes. The convergent parallel mixed methods component refers to the integration of both quantitative and qualitative data collection methods to complete the process evaluation at the same time. The process indicators reflect the immediate outputs of the data use initiatives. In line with existing evidence on intervention uptake and sustainability, the process evaluation will elucidate how the initiatives have been implemented in the intervention councils and why [21, 27–31]. In turn, this information will be used to explain the probable heterogeneity of effects observed when measuring the effect of the program. Triangulation of data from multiple sources will be done to generate comprehensive information from this study and generate very informative body of knowledge to inform data use related policies and guidelines in the primary health care settings. All the above activities will be guided by the initial TOC developed in this study.

Data will be collected from health managers and frontline workers delivering services in health facilities. Quantitative data collection will be done using structured questionnaire to health care managers and frontline health workers who produce data at multiple points and a document review checklist in order to assesses both the implementation outcomes (acceptability and fidelity) and service outcomes (efficiency, safety and patient centeredness).

The specific research questions in this component will be as follows:

To what extent the data use initiative has been adopted, accepted and maintained?How many users of primary health facility have been reached by the initiative?To what extent do the implementers and beneficiaries of the initiative adhere to the initiative protocol?Is data use initiative faced with implementation challenges? What are those challenges and how can they be addressed?

To answer the above research questions, the following objectives will have to be addressed

To assess the extent of adoption of the data use initiativesTo determine number or proportion of beneficiaries reached by the data use initiativeTo assess the fidelity to data use initiative protocol and SOPsTo assess acceptability of the data use initiative by primary beneficiaries and other stakeholdersTo assess sustainability of the data use initiative in the intervened primary health facilitiesTo determine the implementation challenges and success of the data use initiativesUnderstand the effects of the data use initiative on health system and patient outcomes

To understand the effects of the data use initiative, we will collect data at baseline and end line in order to allow two points measures of the outcome data. In this step, to assess compliance to national and international quality standards, the study team will rely both on the analysis of the routine health information system (at the facility level and district level) and information collected from respondents. Specific research questions include, i) has the quality of primary health facility data improved following implementation of the initiative? ii) What factors have contributed to the observed changes?

Specific objectives:-

Assess the effect/impact of data use initiative on beneficiaries’ capabilities (knowledge, and skills to analyze and interpret data)To evaluate the impact/effect of data use initiative on the quality of data collected in the primary health facilitiesTo determine the impact/effect of the initiative on the use of data for decision making and planningTo evaluate the effect of data use initiative on the performance of primary health facilities in terms of quality of delivered health services (availability drugs, medical supplies and equipment) and client’s satisfaction with the services.

*Study component 1*: *Measuring effects of the data use initiative*. This component aims at establishing the effects of data use initiatives on quality of care and selected health outcomes. To establish and control the counterfactual, data will be collected in the intervention and control councils. This component comprises collection of quantitative and qualitative data at two points (baseline and end line) covering a period of one year.

*Sampling and sample sizes*. This component will collect information from health facility documents , health care workers, and patients. The samples and sample sizes for this quantitative component are as follows

We will collect health facility level data to assess the overall situation of quality of care from a total of 80 health facilities (40 from intervention health facilities & 40 from control health facilities).From each of the selected health facilities we will collect quantitative data from at least five participants (the chairperson of the health facility governing committee, in charge of the health facility, data focal person , in charge of RMNCAH services and in charge of outpatient services) making a total of 400 participants. This sample is adequate to conduct robust inferential analyses related to the effects of the data use initiative. Moreover, taking p = 50% and applying Cochrane formula while also accounting for refusals and the fact that some health facilities (especially the dispensaries) may not all the five staff, an addition of 10% to the minimum sample will be added to reach 440 participants.Also, from the selected facilities exiting patients will be systematically selected after gender stratification following medical consultations. The exit interview with Client/patients will be approached after they have received the services and are ready to go home. Respondents eligible for interview include all exiting patients or relatives of patients (aged above 18 years). They will be sampled to ensure equal numbers of men and women are captured. The sample is calculated using the Cochran formula (1977) [32]; by taking 50% as a proportion of patients’ perception on quality of primary health care services) and a power of 80% allowing for an estimated error margin of 5%, the sample size obtained was 384 patients. To account for refusals, an additional 10% of the sample will be added (n = 38), making a total of 422 patients.

The qualitative samples and sample sizes for this component are as follows:

We will use purposive sampling technique, to select at least 8 participants for in-depth interviews as a sub-sample of exit interview questionnaire (for exiting patients) from each district, i.e., 4 participants from dispensaries and four participants from health centers, thus making a total of 64 patients. Also, a total of 4 health care workers will purposively be selected for in-depth interview per council, i.e., 2 participants from dispensaries and 2 participants from health centers, thus making a total of 32 in-depth interviews. The exact number of interviews will be based on saturation of information that is the sample could even be smaller or increase depending on saturation. The interviews will explore the process and experiential dimension of quality of care and will complement evidence emerging from the quantitative analysis.

*Data collection tools and procedures*. To understand the data use situation including their determinants (governance, technical, behavioral and context) and existing initiatives and the indicators related to quality of care at the health facility, we will rely on facility assessment tool, interviews with clients and a structured questionnaire to health care workers and an observation checklist. The tools aim at getting a holistic picture on changes in quality of care and related health outcomes overtime as the initiative is implemented or as a result of changes in time. The tools are described here under and are found in S2 File.

Facility assessment tool: We will use the star rating tool to understand the baseline situation in relation to quality of care of the health facilities. The star rating tool is a validated instrument that has been used to measure quality of care in the health facilities in Tanzania. We will measure the changes in indicators related health system building block indicators (financing, availability of health commodities, and motivation of human resource for health) that could reflect the effects of data use at health facility level.Patient exit interview questionnaire: We will use a patient exit questionnaire to understand patient’s experiences and perceptions on the quality of care provided in health facilities. These questionnaires are also part of the star rating tool, i.e., we will adopt all the questionnaire in the star rating toolNB: The star rating tool consists of facility assessment and exit interview questions and has been used repeatedly to assess quality of health care services in Tanzania [33]. During the baseline assessment, we will also pilot and validate an organizational readiness tool geared to assess health workers readiness to implement data use interventionsHealth workers questionnaire: We will use a health workers questionnaire to understand the situation in relation to data use and the determinants of data use at the facilityObservation checklist: We will use an observation checklist that aims at getting the reality in relation to data use tools, equipment and practices related to data use at the health facilityFor the health outcomes: we will extract data from DHIS2 for selected indicators using a document review checklist/DHS2 data extraction checklist. The indicators include: Number of health facility deliveries, number of pregnant mothers completed 4th ANC visit, NC Total Pregnant Women (PW) tested, Number of pregnant women who tested positive for HIV (First Test), Proportion of pregnant women on ARV to prevent HIV transmission and Number of Maternal Deaths

*Study component 2*: *Measuring implementation process of the data use initiatives*. This component aims to establish data use initiative implementation processes as well as influencing (moderating) factors. This component will be implemented in the intervention councils to better understand the initiative’s implementation processes, thus unlocking the data use initiative’s black box by better knowing the initiative’s components and contextual impacts.

*Sampling and sample sizes*. Our sample for measuring the implementation process (process evaluation) will include implementers of the data use initiative at the council and health facility level. The participants will be implementing partners, health care mangers and health facility governing committee members (CHMT, HFGCs, health facility-in charges and frontline health workers). The fact that all CHMT members are guardians of data use at the council and its respective health facilities, they will all be included in the study (census) thus making a total of 60 CHMT members i.e., at least 15 members from each of the participating council. At least two members of HFGCs will be recruited in the study making a total of 80 HFGC members. A consecutive sample of health care workers from the participating health facilities with a maximum of five participants based on the assumption that the selected facilities should have a minimum of five health care workers, i.e., a total of 200 health workers will be recruited in the study. In addition, routine health facility files and documents will be read and summarized to fit the study context.

*Data collection tools and procedures*. The domains for the implementation process evaluation are reach, adoption, fidelity of implementation, acceptability and sustainability. Data will be collected from the following types of participants and documents; implementing partners, health care managers and health facility governing committee members (CHMT, HFGCs, health facility -in charges and frontline health workers) and health facility documents. Table 1 provides the details on the set of tools and their alignment to objectives and sources of data. In line with our mixed methods design, quantitative data will be gathered using; structured questionnaires, document review/ observation checklists, and semi-structured in-depth interviews (IDIs).

**Table 1 pone.0303552.t001:** The set of tools and their alignment to objectives and sources of data.

Study component	Objective	Domain/ Data required	Sources of data	Data collection tools
Development of a Theory of change	Develop a theory of change (TOC) for data use initiatives and document the process under which such a TOC is developed		Documents, participants (data use initiative designers and implementers)	Document review checklist, Semi structured interview guides for in-depth interview
Baseline evaluation	Understand the initial (baseline) situation of data use in the study settings in relation to decision making and comprehensive (council or health facility) planning	Socio-demographic characteristics Governance for data use Data use behaviors Equipment and tools for data use Contextual factors for data use	Documents, participants (health facility managers, health care workers, district managers/CHMT members) and members of Health facility governing committees	Document review checklist, Structured questionnaire, semi structured interview guides for in-depth interview
Process evaluation	1) To determine the adoption of data use initiative by the health workers	Uptake of the data use initiative by the implementers (proportion and representativeness of individuals involved in implementing the initiative) [ADOPTION]	Documents, participants (health facility managers, health care workers, district managers/ CHMT members) and members of Health facility governing committees	Document review checklist, structured questionnaire, Semi structured interview guides for in-depth interview
	2) To determine the reach of the data use initiative to health workers at the CHMT and the health facility level	The proportion of health care workers reached by the initiative [REACH]	Documents, participants (health facility managers, health care workers, district managers/ CHMT members) and members of Health facility governing committees	Document review checklist, structured questionnaire, Semi structured interview guides for in-depth interview
	3) To assess the fidelity to data use initiative protocol and SOPs	The extent to which the implementers adhered to the original plan to implement all the essential elements of the program; any deviations or adaptations to the original plan, and follow-up activities [FIDELITY OF IMPLEMENTATION]	Documents, participants (health facility managers, health care workers, district managers/CHMT members) and members of Health facility governing committees	Document review checklist, structured questionnaire, Semi structured interview guides for in-depth interview
	4) To assess acceptability of the data use initiative by primary beneficiaries and other stakeholders	Information on affective attitude, burden, ethicality, intervention coherence, opportunity costs, perceived effectiveness and self-efficacy [ACCEPTABILITY]	Documents, participants (health facility managers, health care workers, district managers/CHMT members) and members of Health facility governing committees	Document review checklist, structured questionnaire, semi structured interview guides for in-depth interview
	5) To determine the extent to which the data use practices become part of the routine health facility practices and maintain its effectiveness	Maintenance/ sustainability	Documents, participants (health facility managers, health care workers, district managers/CHMT members) and members of Health facility governing committees	Document review checklist, structured questionnaire, semi structured interview guides for in-depth interview and FGD
	6) To determine the implementation challenges and success of the data use initiatives	Contextual factors	Documents, participants (health facility managers, health care workers, district managers/CHMT members) and members of Health facility governing committees	Document review checklist, structured questionnaire, Semi structured interview guides for in-depth interview and FGD
Outcome evaluation	1) Assess the effect/impact of data use initiative on beneficiaries’ capabilities (knowledge, and skills to analyse and interpret data)	impact of data use (knowledge, skills)	Documents, participants (health facility managers, health care workers, district managers/CHMT members) and members of Health facility governing committees	Document review checklist, structured questionnaire, Semi structured interview guides for in-depth interview
	2) To evaluate the impact/effect of data use initiative on the quality of data collected in the primary health facilities	impact of data quality (relevance; accuracy; credibility; timeliness; accessibility; interpretability; and coherence)	Documents, participants (health facility managers, health care workers, district managers/ CHMT members) and members of Health facility governing committees	Document review checklist, structured questionnaire, semi structured interview guides for in-depth interview
	3) To determine the impact/effect of the initiative on the use of data for decision making and planning		Documents, participants (health facility managers, health care workers, district managers/ CHMT members) and members of Health facility governing committees	Document review checklist, structured questionnaire, semi structured interview guides for in-depth interview and FGD
	4) To evaluate the effect of data use initiative on the performance of primary health facilities in terms of quality of delivered health services (availability drugs, medical supplies and equipment) and client’s satisfaction with the services.	availability of health system inputs, health system outcomes (responsiveness, quality of care and utilization of services) and client satisfaction	Documents, participants (health facility managers, health care workers, district managers/CHMT members) and members of Health facility governing committees	Document review checklist, structured questionnaire, Semi structured interview guides for in-depth interview
	5) To evaluate the effect of data use initiative health outcomes	Patient pathways, patient outcomes	Documents, participants (health facility managers, health care workers, district managers/CHMT members) and members of Health facility governing committees	DHIS extraction form, Document review checklist, structured questionnaire, semi structured interview guides for in-depth interview
	6) To determine the factors influencing the observed change in outcomes	Contextual factors	Documents, participants (health facility managers, health care workers, district managers/ CHMT members) and members of Health facility governing committees	Document review checklist, Semi structured interview guides for in-depth interview

The questionnaire for health workers will capture information related to socio-demographics, general knowledge on data use initiative, acceptability of the initiative to health workers, fidelity of implementation, sustainability of data use initiative and moderating factors. The questions in this tool will either be multiple choice, yes/no or Likert scale.

A structured observation checklist will be used to collect data on implementation of data use initiative. This will serve as triangulation of the information obtained from the health care workers. We will use semi structured instruments to collect data from the implementing partners, health care mangers at all levels and frontline health workers. The qualitative component aims at uncovering the participant’s experiences with data use and their expectations on the data use initiatives and its future maintenance at the health facility. All the tools to be used in this study are detailed in S2 File.

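### The 384 exit patients are a single-proportion precision size with no power term, so the stated 80% power is unsupported, as is the claim that 400 health workers suffice for effect inference

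*Protocol article*

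**What the plan says.** All the sample-size statements are in the protocol article, study component 1, under sampling and sample sizes.

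- **Exit patients.** The article names the Cochran formula, "by taking 50% as a proportion of patients’ perception on quality of primary health care services", and then gives "a power of 80% allowing for an estimated error margin of 5%, the sample size obtained was 384 patients". For refusals, "an additional 10% of the sample will be added (n = 38), making a total of 422 patients".
- **Health workers.** At least five participants in each of 80 facilities gives 400. Of this number the article says: "This sample is adequate to conduct robust inferential analyses related to the effects of the data use initiative". It then adds support by "taking p = 50% and applying Cochrane formula while also accounting for refusals" and by noting that some facilities may lack all five staff, and concludes with "an addition of 10% to the minimum sample will be added to reach 440 participants".
- **Design.** The study design section describes a controlled before-and-after comparison to estimate the effects of the initiative. Study component 1 sets data collection at baseline and end line, in "80 health facilities (40 from intervention health facilities & 40 from control health facilities"). Table 2 lists 440 health workers and 422 exit patients as the effects-measurement samples for the structured questionnaire, with regression and paired t tests between baseline and end line among the analyses.

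**The concern.** Power is the probability of detecting a named effect with a named test. A Cochran calculation has neither: it fixes the width of a confidence interval around one proportion. A power figure attached to its result therefore describes nothing that was calculated.

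The sample is used for something else, namely a contrast between two groups of facilities, across two rounds, with patients nested in facilities. Such a contrast is estimated much less precisely than one pooled proportion. A reader who takes the 80% at face value, with the 5-point margin as the only quantity beside it, would think the patient survey could reliably show changes of about that size. A null result could then be read as evidence that the initiative does not work.

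The adequacy sentence for health workers has the same weakness. It makes a claim about inference on effects, and no effect size, margin or variance is given to support it.

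**Working it through.** **1. Reproduce the stated patient figure.** Inputs from the article: p = 0.50, margin e = 0.05. Assumed: 95% confidence, z = 1.96.

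n = z² p(1 − p) / e² = 1.96² × 0.25 / 0.0025 = 384.

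Adding 10%: 384 + 38 = 422. Both stated figures reproduce exactly, and 80% power is used nowhere.

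**2. Put a power term in.** One sample, 5-point departure, two-sided 5%, 80% power:

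n = (1.96 + 0.8416)² × 0.25 / 0.0025 ≈ 785.

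Power at n = 384 for 5 points: standard error 0.5/√384 = 0.0255; 0.05/0.0255 − 1.96 ≈ 0; Φ(0) ≈ 50%. A one-sided version needs about 618. A two-arm comparison of 50% with 55% needs about 1,565 per arm. None of these gives 384.

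**3. Health workers.** 80 × 5 = 400 and 400 × 1.1 = 440. The Cochran formula with p = 50% and a 5-point margin would give 384. The 440 is therefore the facility count times five plus 10%; the formula did not generate it.

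**4. Per-arm precision for patients.** With 384 split equally (192 per arm): 1.96 × √(0.25/192) = ±7.1 points. With 422 (211 per arm): ±6.7 points. These hold for one round, ignoring clustering.

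**5. Detectable net change for patients.** The measure is a difference-in-differences. Assumptions, none stated in the article: binary outcome near 50%, two-sided 5%, 80% power, equal split between arms, different patients in each round. The variance with n per arm per round is 4 × 0.25 / n = 1/n, so the detectable net change is 2.8016 × √(1/n).

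| Reading of the patient sample | n per arm per round | Detectable net change, no clustering |
|---|---|---|
| 422 per round | 211 | 19.3 points |
| 384 per round | 192 | 20.2 points |
| 422 over both rounds | 105.5 | 27.3 points |
| 384 over both rounds | 96 | 28.6 points |

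At 192 per arm per round (standard error 0.0722), power is Φ(0.05/0.0722 − 1.96) ≈ 10% for 5 points and Φ(0.10/0.0722 − 1.96) ≈ 28% for 10 points. At 211 it is about 11% and 31%.

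**6. Allow for facilities.** With m patients per facility per round and a facility-level correlation between rounds of CAC, the variance is multiplied by (1 − ICC) + m × ICC × (1 − CAC). Neither ICC nor CAC is in the article; ICC 0.05 to 0.20 and CAC 0 to 1 are assumed as a range. Here m is 384/80 = 4.8 or 422/80 = 5.275.

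| ICC | CAC | m = 4.8 (384 per round) | m = 5.275 (422 per round) |
|---|---|---|---|
| 0.05 | 0 | factor 1.19, 22.1 points | 1.21, 21.2 points |
| 0.20 | 0 | 1.76, 26.8 points | 1.86, 26.3 points |
| 0.05 | 1 | 0.95, 19.7 points | 0.95, 18.8 points |
| 0.20 | 1 | 0.80, 18.1 points | 0.80, 17.3 points |

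The range is about 17 to 27 points. At CAC = 0.8 the factor is close to 1 throughout, and the figure stays at 19 to 20 points.

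**The case against.** The best defence is that every stated number reproduces, so the fault is a wrong label and not wrong arithmetic. That is correct. It is also true that an article may leave the ICC, the significance level and the between-arm effect to a fuller document, so their absence is not the point. What stands against the text is what it asserts: a power that was not calculated, and an adequacy for effect inference with no basis given. One could add that any sample has 80% power for some effect. But none is named, and at the only quantity given, 5 points, the statement is false.

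A reader might go further in several ways that the article does not support:

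- **That the whole study is said to have 80% power.** The phrase belongs to the patient sample only; the adequacy sentence belongs to the health workers.
- **That health workers cannot exceed 400, so 440 is impossible.** The text asks for at least five per facility. Five posts are listed, but the number is a floor, and larger facilities may supply more.
- **That 440 should have been 422.** The 400 already exceeds the Cochran 384, and adding 10% to 400 is coherent.
- **That the refusal allowance is wrong because 384/0.9 = 427.** The article says that 10% of the sample is added, and does so. Even with 10% refusals, 380 patients remain and the margin moves from 5.00 to 5.03 points.
- **That clustering must raise the detectable change.** The same facilities are followed for a year, so stable facility differences partly cancel between rounds, and the figure can fall slightly.

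The net-change figures also assume an unadjusted binary outcome. The article lists t tests, paired t tests, regression and Likert items, so other outcomes would have other figures.

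**Conclusion.** The concern holds as a misstatement of what the sample size is. The 384 is a precision size for one pooled proportion, and the 80% power attached to it is not a property of that calculation or of this two-arm, two-round design. The adequacy claim for 400 health workers is likewise unsupported on the page.

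The size of the gap depends on assumptions that the article does not give, but the conclusion does not: across every case computed, the detectable net change is at least about 17 points, more than three times the 5 points stated. This does not show that the samples are too small for the study's purpose, because the article names no target effect against which to judge them.

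**What to change.** Text changes only, in the sampling section of study component 1:

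1. Delete the power phrase and describe 384 as the size for a 95% interval of ±5 points around a single proportion, with 10% added to reach 422.
2. Remove the adequacy sentence for health workers, or support it with a named effect and its assumptions.
3. Say that 440 is 80 × 5 plus 10% and is not a Cochran result.
4. State whether 422 and 440 are per round or cover both rounds.
5. Give the per-arm precision for patients, about ±7 points per round before clustering (if 422 is per round).
6. Give the minimum detectable net change for patients with its assumptions: about 19 to 20 points unclustered if 422 is per round; roughly 17 to 27 points for ICC 0.05 to 0.20, depending on how far facility effects persist between rounds; about 27 to 29 points unclustered if 422 covers both rounds.

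No extra recruitment is needed. The cost is that the stated figures become less favourable than the present wording suggests.
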